#### Control group

Participants in the control group will be placed on a waiting list for 6 months. They will not be restricted from seeking other forms of treatment during the waiting period, nor from using sleep medications. After the waiting period, they will have the possibility to participate in the treatment at their Healthy Life Centre, which will be offered to them by a Healthy Life Centre employee during the waiting period.

### Assessments

Assessments will be carried out at 6 different time points during the RCT: T1, prior to the intervention; T2, immediately post-intervention; T3, 3 months post-intervention (primary outcome measurement); T4, 6 months post-intervention; T5, 1-year post-intervention; and T6, 2 years post-intervention. The primary outcome is self-reported insomnia severity assessed by the ISI. Several other outcomes will be used in analyses of secondary outcomes, moderators and exploratory mediators, resource use and work productivity, and in a mixed-method process evaluation, described below. Descriptions of all measures, objectives of their use, collected, the participant group receiving them, and the objectives of their use, are provided in Table 2.

**Table 2 Tab2:** Overview of the assessments utilized in the randomized controlled trial

Objective	Measure	Measurement timepoint	Participant group
Demographic information	Self-rated custom questions	T1	All
Primary outcome	Insomnia severity (Insomnia severity index)	Screening, T1, T2, T3, T4	
Secondary outcomes	Health-related quality of life (EuroQol EQ5D-5L)	T1, T2, T3, T4	
	Fatigue (Chalder Fatigue Scale)	T1, T2, T3, T4	
	Mental distress (Hopkins Symptoms Checklist)	T1, T2, T3, T4	
Moderator	Chronotype (Brief Horne-Östberg Morningness-Eveningness Questionnaire)	T1, T2, T3, T4	
Mediators	Unhelpful beliefs about sleep (Dysfunctional Beliefs and Attitudes about Sleep questionnaire-16)	T1, T2, T3, T4	
	Sleep reactivity (Ford Insomnia Response to Stress Test)	T1, T2, T3, T4	
Subjective assessment of sleep patterns	7-day sleep diary	T1, T2, T3, T4	
Mixed-method process evaluation of facilitators and barriers of participants’ treatment adherence in group-delivered CBT-I	Motivation for treatment (Nijmegen Motivation List 2)	T1	~ 60 intervention group participants
	Treatment credibility (Credibility / Expectancy Questionnaire)	T1	
	Adherence to CBT-I components (Treatment Components Adherence Scale)	T3	
	Evaluation of treatment (CBT-I evaluation scale)	T3	
	Individual semi-structured interviews	T2, T3	10–12 intervention group participants
Evaluation of sick leave rates, medication use, and healthcare services utilization	Norwegian Patient Registry	T5, T6	All intervention group participants
	Norwegian Prescription Database	T5, T6	
	National Insurance Administration	T5, T6	

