**Methods:**

A pragmatic multicentre randomized controlled trial will be conducted with about 300 participants recruited across 26 Healthy Life Centres in Norway. Participants will complete online screening and provide consent before enrolment. Those who meet the eligibility criteria will be randomized to a group-delivered CBT-I or to a waiting list according to a 2:1 ratio. The intervention consists of four two-hour sessions. Assessments will be performed at baseline, 4 weeks, 3- and 6 months post-intervention, respectively. The primary outcome is self-reported insomnia severity at 3 months post-intervention. Secondary outcomes include health-related quality of life, fatigue, mental distress, dysfunctional beliefs and attitudes about sleep, sleep reactivity, 7-day sleep diaries, and data obtained from national health registries (sick leave, use of relevant prescribed medications, healthcare utilization). Exploratory analyses will identify factors influencing treatment effectiveness, and we will conduct a mixed-method process evaluation to identify facilitators and barriers of participants’ treatment adherence. The study protocol was approved by the Regional Committee for Medical and Health Research ethics in Mid-Norway (ID 465241).

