**Discussion:**

This large-scale pragmatic trial will investigate the effectiveness of group-delivered cognitive behavioural therapy versus waiting list in the treatment of insomnia, generating findings that are generalizable to day-to-day treatment of insomnia in interdisciplinary primary care services. The trial will identify those who would benefit from the group-delivered therapy, and will investigate the rates of sick leave, medication use, and healthcare utilization among adults who undergo the group-delivered therapy.

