### Aims

The primary aim is to conduct a pragmatic, multicentre randomized controlled trial (RCT) to investigate the effectiveness of group-delivered CBT-I in primary care on insomnia severity at 3 months post-treatment. Secondary aims include:i.Investigate the effectiveness of group-delivered CBT-I on health-related quality of life, fatigue, mental distress, and sleep diary data at 3- and 6-months post-treatment.ii.Investigate whether potential treatment moderators (e.g., chronotype, reactivity to stress, duration of insomnia, length of prior insomnia treatment, treatment group size, physical activity) influence the effectiveness of group-delivered CBT-I.iii.Compare sick leave days, use of relevant prescribed medication (e.g., psychotropics, sedatives) and healthcare resource utilization, utilizing national registry data at pre-treatment vs. 1- and 2-years post-treatment.iv.Conduct exploratory mediation analyses to identify mechanisms behind change in the primary and secondary outcomes, focusing on psychological measures of beliefs about sleep, reactivity to stress, and sleep-related self-efficacy as potential mediators.v.Conduct a mixed-method process evaluation to assess facilitators and barriers of participants’ treatment adherence.

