#### Eligibility and procedure

All adults interested in participation will enter a secure online screening portal, through a link on the project’s webpage. The screening portal includes a series of self-rating questions pertaining to the eligibility criteria. Inclusion criteria include age ≥ 18 and Insomnia Severity Index (ISI) score ≥ 12, indicating insomnia symptoms with a significant impact on the individual [19]. Since this is a pragmatic trial, we will only exclude adults with diagnosed major psychiatric, somatic, or neurological disorders for which CBT-I may be contraindicated (see Fig. 1). All potential participants will have to confirm their proficiency in the Norwegian language.

The researchers will evaluate inclusion criteria of each potential participant. Eligible participants will be sent a digital consent form. After consenting, participants will be randomized, and thereafter informed of allocation outcome. Participants in the treatment group will be contacted by the respective Healthy Life Centre employees about the next available treatment group. If they cannot participate (i.e., the time or location of treatment group does not align with participants’ schedule), they will be excluded. All participants will obtain invitations to complete questionnaire batteries and sleep diaries via e-mail at four measurement timepoints (see Fig. 1). Non-responders will receive reminders via SMS or phone call. Those who still do not respond will be followed up by phone and asked instead to report only on the primary outcome measure (ISI).

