#### Resource use and work productivity

We will access national health registry data at T5 and T6, to collect information on the short- and medium-term impact of group-delivered CBT-I on rates of sick leave (accessed from the National Insurance Administration), as well as relevant medication (obtained from the Norwegian Prescription Database) and health resource utilization (obtained from the Norwegian Patient Registry). Linkage to the registry data will be based on the social security number of each participant.

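### Registry outcomes are planned as a before-after comparison in the intervention arm only, yet are described as the impact of CBT-I and as secondary outcomes of the randomised trial

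*Protocol article*

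**What the plan says.** The article describes the registry outcomes in six places.

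- **Assessments, Table 2.** The three registries, at T5 and T6 (1 and 2 years), have the participant group "All intervention group participants". The same column uses *All* for measures collected in both arms. The registries stand under an objective of their own, not in the secondary-outcome rows.
- **Aims, item iii.** The comparison is made "utilizing national registry data at pre-treatment vs. 1- and 2-years post-treatment". No between-arm contrast is named.
- **Abstract, Discussion.** The trial will investigate "the rates of sick leave, medication use, and healthcare utilization among adults who undergo the group-delivered therapy".
- **Resource use and work productivity.** The purpose is to "collect information on the short- and medium-term impact of group-delivered CBT-I on rates of sick leave", with medication and health resource use alongside. The section adds: "Linkage to the registry data will be based on the social security number of each participant".
- **Abstract, Methods.** The secondary outcomes include "data obtained from national health registries (sick leave, use of relevant prescribed medications, healthcare utilization").
- **Statistical analysis plan section.** Continuous and binary secondary outcomes get mixed models with time, group, their interaction and baseline covariates.

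The limitations in the main Discussion do not mention an uncontrolled registry comparison.

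**The concern.** The trial has a randomised control arm, but the registry outcomes as laid out in Table 2 and aim iii do not use it. Participants enter with an "Insomnia Severity Index (ISI) score ≥ 12", and the Monitoring section says that all of them are seeking treatment. If registry outcomes also run high around entry, some later fall would be expected without any treatment. Secular trend, ageing and other treatment over one to two years would also be absorbed into the change.

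At stake is what a fall in sick leave, prescriptions or consultations would be taken to mean. Under the label of impact, and listed as a secondary outcome of a randomised trial, a reader would credit it to CBT-I, although the comparison does not have the protection of randomisation.

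**Working it through.** **1. Do the places agree?** The article gives no figure for the registry analyses, so there is none to reproduce. The comparison is of text.

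| Place | Arms | Contrast or claim |
|---|---|---|
| Table 2 | Intervention only | 1 and 2 years |
| Aims, iii | Not stated | Pre- versus post-treatment |
| Abstract, Discussion | Those who undergo therapy | Rates |
| Resource use section | Linkage key for each participant | Impact of CBT-I |
| Abstract, Methods | Trial secondary outcome | Not stated |
| Statistical analysis plan section | Both (group term) | Time by group |

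The first three rows fit an intervention-only before-after design. The last two need both arms: with intervention data alone, neither the group term nor the interaction can be estimated. The fourth makes a causal claim that the first three cannot carry.

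**2. Is change without treatment plausible here?** The Sample size section gives mean ISI changes in earlier trials of 6.2 points (intervention) and 1.4 points (control). So 1.4 / 6.2 = 23% of the treated arm's change also occurred in controls. A before-after reading would give 6.2 points where the controlled difference is 6.2 − 1.4 = 4.8. This concerns ISI; the article has no such figure for registry outcomes.

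**3. How large could the effect on a test be?** This is an illustration only. Suppose the pre-treatment mean lies a SD above the long-run mean, the pre/post correlation is r, and treatment does nothing.

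- Expected fall = a(1 − r).
- SE of the mean change = √(2(1 − r)/n), with n = 194 (planned intervention arm, Sample size section).
- z = fall / SE; two-sided rejection probability = Φ(z − 1.96) + Φ(−z − 1.96).

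Example: a = 0.3, r = 0.5. Fall = 0.15; SE = √(1/194) = 0.0718; z = 2.09; rejection 55%.

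| a (assumed) | r = 0.3 | r = 0.5 | r = 0.7 |
|---|---|---|---|
| 0 | 5% | 5% | 5% |
| 0.1 | 13% | 11% | 8% |
| 0.2 | 38% | 29% | 19% |
| 0.3 | 70% | 55% | 37% |
| 0.4 | 91% | 80% | 58% |

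Both a and r are assumptions.

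**4. What would a randomised registry contrast resolve?** With 98 controls and 194 intervention participants, the noncentrality is d√(98 × 194 / 292) = 8.07d. A two-sided 5% t-test then has 80% power at d = 0.35 (8.07 × 0.348 = 2.81) and 90% power at d = 0.40 (8.07 × 0.403 = 3.25). This assumes a continuous outcome, complete linkage and no gain from baseline adjustment.

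**The case against.** The strongest reply is that the text is not settled. Aim iii names a time contrast and never says that it is single-group. Linkage is described for each participant, and the abstract and the analysis section together would allow a between-arm model. This stands in part, and it is why the point is a conflict to reconcile as well as a design weakness. It does not remove the weakness: the linkage sentence describes the key and states no comparison, and Table 2 is the one place that says which arm supplies the data. An analysis plan not shown here could add a between-arm contrast only if control data are collected.

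A second reply is that the aim is descriptive, as the abstract's Discussion suggests. That is fair, and a before-after rate can be reported as such. A reader might go further and call the registry results uninterpretable; the documents do not support that. What fails is the effect claim.

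Third, the rejection rates rest on invented inputs. Participants are selected on ISI, not on sick leave or prescriptions, so any excess at entry in registry outcomes is indirect and could be nil. The article also specifies no before-after significance test, and sick-leave days and service counts need not behave like a simple mean change. It would be wrong to quote 55%, or any other cell, as the false-positive rate of this plan.

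Fourth, controls would not supply an untreated comparator at 1 and 2 years, because they may take up treatment after the 6-month wait (Control group section). This is correct and limits what the fix can deliver. Nor is the waiting period a clean main contrast: the offer to controls is made during it, and the Monitoring section allows intervention participants to wait up to 6 months themselves, although waits over 3 months should be rare.

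**Conclusion.** The point holds. Table 2 and aim iii, read together, give an intervention-only before-after comparison. The Resource use section, the abstract's Methods and the analysis section describe the same data in terms that need a comparator. Followed as Table 2 has it, the plan would support a statement about change in treated participants, not about the effect of CBT-I.

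The size of any bias cannot be derived from the documents. The range of 5% to about 91% in the working shows only that the answer depends on entry excess and correlation, neither of which is known. The conclusion about design needs no particular value, since secular trend, ageing and other treatment are uncontrolled even with no excess at entry. The omission from the limitations is a separate, smaller fault.

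**What to change.** 1. In Table 2, change the participant group for the three registries to *All*. Extract the same data for controls, with the randomisation date as index in both arms.
2. Analyse as randomised, adjusting for each person's pre-randomisation registry value. State in aim iii and the Resource use section that the 1- and 2-year contrasts compare immediate with delayed offer of treatment.
3. Report the waiting-period contrast as supportive only, because intervention-arm waiting time dilutes it. Keep the before-after comparison as descriptive.
4. If control consent does not cover linkage, replace *impact* with *change*, drop effect claims, stop listing the registry data among outcomes analysed with group terms, and add the uncontrolled comparison to the limitations.

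The cost is an extension of the registry and ethics approvals and a check of control consent, with no burden on participants. The price in interpretation is that a randomised immediate-versus-delayed contrast at 1 and 2 years is expected to be smaller than a treated-versus-untreated one, so it may fall below the d of 0.35 to 0.40 that the planned arms could detect. Item 4 costs only a change of wording.

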#### Demographic questionnaire

The demographic questionnaire includes questions on age, sex, pregnancy in women, highest achieved education level, marital status, children in the household below and over 6 years, occupational status and work ability, shift work, weight and height, physical activity, frequency of muscle pain, use of alcohol and illegal substances, as well as questions about recruitment location, duration of participants’ sleep problems and prior insomnia treatment.

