### Data management and auditing

All self-reported health information will be distributed and collected using the previously described eForsk platform. Upon randomization of each participant, researchers will share an interactive document including participant name, date of birth, phone number and randomization outcome, with the Healthy Life Centre employee to which the participant belongs. In the document, the Healthy Life Centre employee will fill out the date for treatment initiation. Researchers will use this date to plan the distribution of self-report questionnaires. Each Healthy Life Centre will have their own interactive document. Each document will be password protected and shared only with the Healthy Life Centre employees involved in the study.

Upon completion of data collection, an anonymized database will be exported from eForsk, sufficiently encrypted, and stored within the NTNU file system. The participant identification key will be confidential and stored within the eForsk database, with only the project leader having access. All data storage and analysis will be conducted according to the regulations by NTNU and will follow the General Data Protection Regulation. Data will not be disclosed to researchers outside the project or transferred to other countries. A data monitoring committee will not be involved in this study, due to the minimal risks associated with the investigated intervention.

Trial conduct will be audited in line with NTNU’s guidelines. This entails the possibility of an internal quality-assuring control where project information, data management systems, formal approvals, protocol amendments, etc. may be audited. Moreover, two independent project members are employed to follow data collection and management, and to provide support to any participants experiencing issues with the data collection. These project members have regular contact with the Healthy Life Centres participating in the trial. Both the project members and the project leader are informed about withdrawals from the study, and possible adverse events are reported to the Healthy Life Centre employees by the participants.

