#### Statistical analysis plan

A detailed statistical analysis plan will be published before unblinding of study data. Descriptive statistics will be presented stratified by group allocation. Categorical and binary variables will be summarized as counts and percentages, while continuous variables as means and standard deviations or medians and interquartile range, as appropriate.

The primary outcome will be analyzed using the intention-to-treat principle. Linear mixed models will be used to estimate the mean differences between T1 and T3 in ISI with 95% confidence intervals between the two groups. For continuous secondary outcomes, linear mixed models will be utilized, while binary secondary outcomes (e.g., clinically relevant change in ISI) will be analyzed using logistic mixed models. Models will include time, group, time–group interaction and baseline covariates. Since we expect that some intervention group participants will miss some treatment sessions, per-protocol analyses will be used for individuals who complete ≥ 3 sessions. Missingness patterns will be investigated, and pattern-mixture models will be used to simulate situations where the data are not missing at random. Interim analyses will not be carried out, due to limited expected adverse effects of the treatment, and because all intervention group participants are followed up by the Healthy Life Centre employees during the treatment.

Moderation analyses will be conducted to investigate whether demographics (e.g., age, sex) chronotype, treatment group size, physical activity, length of prior insomnia treatment, and duration of insomnia moderate the effectiveness of group-delivered CBT-I on primary and secondary outcomes. Exploratory mediation analyses will be conducted to investigate mechanisms of change in the primary and secondary outcomes, focusing on psychological measures of beliefs about sleep, reactivity to stress, and sleep-related self-efficacy.

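### The demographic form, given only at T1, is answered after participants know their arm, so three planned moderators and any covariate taken from it are post-allocation measurements

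*Protocol article*

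**What the plan says.** All places are in the protocol article.

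- **Order of events (Eligibility and procedure).** "After consenting, participants will be randomized, and thereafter informed of allocation outcome". Before that step there is only online screening: "The screening portal includes a series of self-rating questions pertaining to the eligibility criteria". The questionnaires are described after disclosure: "All participants will obtain invitations to complete questionnaire batteries and sleep diaries via e-mail at four measurement timepoints".
- **Scheduling (Data management and auditing).** On randomisation the centre receives the allocation and enters a treatment start date. "Researchers will use this date to plan the distribution of self-report questionnaires".
- **Timing of T1 (Assessments, Table 2).** T1 is defined relative to the start of the intervention, not to randomisation. The demographic questions appear at T1 only. The ISI is taken at screening and at T1 to T4.
- **Content (Demographic questionnaire).** The form covers education, physical activity and, among other items, "duration of participants’ sleep problems and prior insomnia treatment". Statistical analysis plan lists physical activity, length of prior insomnia treatment and insomnia duration as moderators.
- **Phone rescue (Eligibility and procedure).** Persistent non-responders are "followed up by phone and asked instead to report only on the primary outcome measure (ISI").
- **Model (Statistical analysis plan).** "Models will include time, group, time–group interaction and baseline covariates". The covariates are not named, and a detailed analysis plan is announced.
- **Between allocation and treatment.** Control group says of waiting-list participants: "They will not be restricted from seeking other forms of treatment during the waiting period". Monitoring allows intervention participants a wait of up to 6 months, with more than 3 months expected only rarely.

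**The concern.** A moderator should be fixed before allocation. If it can respond to the arm, an interaction with arm mixes true effect modification with behaviour or reporting that followed randomisation. Here a participant who has just been told to wait, or has just been offered a group, is asked about earlier treatment and current activity. No later choice of model can turn those answers into pre-randomisation data.

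A second consequence concerns missing values. The form is not repeated, and the phone call recovers the ISI alone. A person who never returned T1 can therefore have outcome data but no value for any variable on that form. A mixed model tolerates missing outcomes, but in its usual form it drops records with a missing covariate. At stake are chiefly the moderation results and, under conditions the article does not state, part of the primary analysis set.

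**Working it through.** **1. Is T1 after disclosure?** Four places agree.
- Eligibility and procedure puts consent, randomisation and disclosure in that order, with only eligibility items beforehand.
- Data management and auditing schedules questionnaires from a date entered after randomisation.
- Table 2 sends two T1 process-evaluation forms to about 60 intervention participants only, so the arm is known by T1.
- Monitoring offers payment for completing T1 to T4 to controls only.

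Fig. 1 is not shown; nothing in the text contradicts this order.

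**2. Which variables are affected?**
- First recorded on the T1-only form: prior insomnia treatment, insomnia duration, physical activity, education and similar items.
- Available without T1: centre (the stratification factor), screening ISI and age (an eligibility item).
- Chronotype is measured at T1 to T4, so it is not a T1-only variable.

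Of the three moderators, length of prior treatment and physical activity can change between allocation and T1. Insomnia duration moves only with elapsed time, though its reporting could still shift.

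**3. Who could be lost from the primary model?** Three conditions must all hold: T1 was never completed, a chosen covariate comes from the T1 form, and cases with a missing covariate are deleted. Someone who completed T1 and is phoned at T2, T3 or T4 already has the covariates and stays in.

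**4. Size if all three hold.** The article gives no T1 non-return rate, so every rate below is an assumption.

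The stated 192 for the primary comparison reproduces: the noncentral t with d = 0.50, two-sided 5% and 2:1 allocation gives 64 + 128 = 192, power 0.901. From the planned 98 + 194 with 30% attrition, 98 × 0.7 ≈ 69 and 194 × 0.7 ≈ 136, or 205 analysed. With a further share m lost for missing covariates:

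| m | control + intervention | power at d = 0.50 |
|---|---|---|
| 0 | 69 + 136 | 0.920 |
| 5% | 65 + 129 | 0.905 |
| 10% | 62 + 122 | 0.890 |
| 20% | 55 + 109 | 0.852 |
| 30% | 48 + 95 | 0.801 |

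The standard error ratio is √[(1/n₁ + 1/n₂)/(1/194 + 1/98)], with n₁ = 194(1 − p_int) and n₂ = 98(1 − p_ctl):
- 5% in both arms: 1.026
- 5% intervention, 15% control: 1.065
- 15% in both arms: 1.085

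The non-returners number 0.05 × 292 = 14.6, 9.7 + 14.7 = 24.4 and 0.15 × 292 = 43.8. Those counts are upper limits, because they credit every non-returner with a T3 ISI. Applying the planned 30% attrition leaves about 10, 17 and 31.

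**5. Bias if non-return differs by arm.** Bias = (p_ctl − p_int) × difference in T3 ISI between non-returners and returners. With 15% against 5% and an assumed 2 points (range 1 to 3), this is 0.10 × 2 = 0.2 points (0.1 to 0.3), towards no effect. The sign reverses if intervention participants skip more. For scale, Sample size implies an SD of (6.2 − 1.4)/0.86 ≈ 5.6, so d = 0.50 is about 2.8 points.

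**The case against.** The strongest reply is that most of this belongs to the announced analysis plan. The covariates are unnamed, and their list and the handling of missing values are ordinary content for that plan. If it chooses centre, screening ISI and age, nobody is lost. This stands. A reader might infer that the primary model discards everyone rescued by phone and so breaks intention-to-treat. The article does not support that: later rescues keep their T1 covariates, and deletion is nowhere written.

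The second reply is that the moderator problem is only possible. The wording and look-back period of the prior-treatment item are not given, long waits are expected to be rare, and the timing of T1 for controls relative to randomisation is not stated. This also stands. It would go too far to say that prior treatment has been shown to be altered by arm, or that controls are told they may seek treatment; the article says only that they are not restricted.

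The third reply is that the assumed pattern of more skipping among controls ignores that only controls are paid to complete T1 to T4. That is fair, and it leaves even the direction of any bias open.

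None of these replies changes the order of events. The form follows disclosure, and an analysis plan cannot alter when it was answered.

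**Conclusion.** The point holds in a limited form. As described, the three T1-only moderators and any covariate from the same form are recorded after participants know their arm. For prior treatment and physical activity this is a real risk to the moderation analyses, of unknown size. For the primary result the effect is probably small and cannot be quantified from the article. It is zero if the covariates are held from before allocation. Under the assumed 5% to 10% extra loss it costs one and a half to three percentage points of power. The conclusion rests on the order of events in the text, with Fig. 1 unseen. The change is worth making because it is cheap, not because the primary analysis is shown to fail.

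**What to change.** - **Participants still to be enrolled:** place the existing demographic form in the eForsk consent step, to be completed before randomisation. Word prior treatment and physical activity as of the screening date.
- **Participants already enrolled:** state that these moderators were measured after allocation, and interpret the moderation results accordingly.
- **Primary model:** use only covariates held for everyone before allocation (centre, screening ISI, age). Otherwise, impute missing baseline covariates ignoring arm. Imputation keeps people in the analysis but does not cure the timing, so the first option is cleaner.

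The cost is a slightly longer form before randomisation, a change to item wording and a sentence in the analysis text. Recruitment began in August 2022, so early and late participants would differ in when the form was completed. That difference should be recorded and reported.
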